### 2.10. Study Variables

Table 1 presents a summary description of the variables collected and the instruments used.

The established cutoff points for specific variables within this protocol are not rigidly fixed and possess inherent flexibility. These thresholds are subject to potential future modifications in subsequent research endeavors. Such adjustments will be driven primarily by the specific aims and hypotheses proposed by the research team, ensuring optimal alignment with evolving research objectives.

The same data collection protocol (including all study variables) applied at baseline (visit 1) will be applied at the 3-month follow-up (intermediate visit 2) and the 6-month post-intervention assessment (final intervention visit 3). Upon completion of the intervention, participants will be instructed to follow their dietary and lifestyle habits without specific restrictions. They will be invited to attend a final data collection session at 12 months (visit 4), i.e., 6 months after visit 3. Once the results of each assessment are available, participants will receive recommendations to consult their primary care physician or emergency services, if necessary.

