Food consumption and nutrient intake: Two methods will be used to assess dietary behavior. First, a 137-item semiquantitative food frequency questionnaire (FFQ) from the PREDIMED Plus study [84] will be administered to assess participants’ habitual dietary intake over the previous year. This FFQ has demonstrated good reproducibility (ICC: 0.63–0.90) and acceptable validity (ICC: 0.40–0.84) for food group assessment in an elderly Spanish Mediterranean population [84]. The validated tool captures the frequency and portion size of a wide variety of foods, including fruits, vegetables, legumes, cereals, dairy products, meats, fish, eggs, nuts, oils, and beverages such as wine, coffee, and soft drinks. The data collected will allow the estimation of energy intake, macronutrients (carbohydrates, proteins, fats), micronutrients (vitamins and minerals), fiber, and bioactive compounds such as polyphenols. Food composition data will be collected from the Spanish Food Composition Database [85] to derive nutrient compositions and estimate total energy intake.

Adherence to the Mediterranean diet: Adherence to the Mediterranean diet (MedDiet) and its specific components will be measured with the Mediterranean Diet Adherence Screener (MEDAS), a Spanish-validated questionnaire that consists of 14 questions [67]. The MEDAS has demonstrated acceptable concurrent validity against a validated FFQ (r = 0.52, ICC = 0.51) in Spanish adults at high cardiovascular risk [86]. The participants will be provided with the MEDAS to complete a tablet, including 12 questions about the frequency of food intake (i.e., olive oil, vegetables, fruit, red meat, animal fats, carbonated beverages, red wine, fish/seafood, nuts, commercial food, and traditional sauces) and 2 questions about food intake habits (i.e., preferred cooking fat used and type of meat consumed) considered characteristic of the Spanish MedDiet. Each question offers two response options, with corresponding scores of 0 (no adherence to the MedDiet component) or 1 (adherence to the MedDiet component).

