#### 2.12.2. Contingency Plan

Recruitment and retention: If enrollment targets are not met, recruitment efforts will expand across the university. These efforts will use multiple communication channels, classroom presentations, and student organizations. If necessary, eligibility criteria may be slightly adjusted with ethical approval. If the number of students who drop out exceeds expectations, retention strategies will be intensified. These strategies include increased contact, flexible scheduling, reminders, small incentives, and feedback on selected results. Participants who are unable to continue in person will be encouraged to complete all self-reported assessments remotely to support intention-to-treat analyses.Intervention delivery: A backup nut supply and alternative suppliers will be maintained. Any adverse reactions will lead to immediate discontinuation and medical referral. Participants for whom poor adherence is detected during the intervention will receive individualized support and encouragement to remain in the study, regardless of their level of adherence.Data collection and analysis: Backup equipment and rescheduling windows will address equipment failure, technician strikes, and other unpredictable circumstances. Missing data, except for covariates, will be handled using multiple imputation and mixed-effects models. Sensitivity analyses will be performed to assess potential bias.External and ethical considerations: In the event of public health emergencies, such as the COVID-19 pandemic that emerged in 2020, assessments will shift to remote formats where feasible. Seasonal and academic calendar effects will be addressed analytically. Any protocol amendments will receive prior ethical approval, and robust procedures are in place to manage data security incidents.Monitoring and quality assurance: Study progress, adherence, retention, and data quality will be monitored monthly by the study coordinator and reviewed quarterly by the principal investigator. Serious adverse events or unexpected issues will prompt immediate review and, if needed, consultation with the ethics committee. Vitamin E (α-tocopherol) levels will be measured in all participants at baseline, 3 months, and 6 months, along with dietary intake assessments. Unauthorized nut consumption in the control group will be detected through either increases in vitamin E levels > 5% from baseline or self-reported nut intake in dietary recalls.Academic stressors and seasonal variations: The following strategies will be adopted to address confounding by academic-related stressors (e.g., examination periods, high academic demands) and seasonal factors: (1) randomization, to balance exposure to stressful periods across groups; (2) tracking assessment dates, to categorize examination periods and seasons; (3) repeated-measures mixed-effects models, adjusting for these factors as covariates; and (4) sensitivity analyses, to test the robustness of findings. Furthermore, stress is directly monitored as a primary outcome using the PSS-10 scale and may reflect partially academic-related stress symptoms.

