Specifically, daily consumption of 30 g of mixed nuts for six months is expected to result in a decrease in the frequency, severity, and number of depressive symptoms and a reduction in anxiety and stress levels, alongside improvements in mental well-being, cognitive function, and sleep quality. The participants who will consume 60 g/day are anticipated to demonstrate a modest increase in these benefits, reflecting a potential dose–response effect. This hypothesis is based on biological plausibility, suggesting that a higher intake of certain compounds (e.g., polyphenols and omega-3 fatty acids) may exert stronger anti-inflammatory, antioxidant and neuroprotective effects required to modulate brain function [19,23]. Additionally, the intervention is expected to improve overall diet quality, maintain body weight (with possible minor reductions in body fat percentage and waist circumference), and enhance metabolic health, including improved lipid profiles, lower blood glucose levels, and reduced inflammatory markers, compared with those of the control group.

This protocol presents several key strengths. First, its randomized controlled design with a dose–response approach addresses a critical evidence gap regarding the “optimal dose” of nut consumption for enhancing mental well-being. Second, the study adopts a multidisciplinary assessment strategy that integrates validated psychometric scales (BDI-II, GAD-7), comprehensive neuropsychological evaluations, and biochemical validation (BDNF). Third, the intervention extends over a six-month period, providing a sufficiently long timeframe to observe meaningful effects. In addition, a fourth visit will be carried out six months after the end of the intervention to evaluate whether nut consumption and its potential effects persist over time. Fourth, adherence will be rigorously monitored through the provision of prepacked nut portions and objective verification via plasma vitamin E levels, thereby increasing compliance in a manner that overcomes challenges typically associated with dietary interventions. Finally, relevant variables (habitual dietary intake, physical activity, fitness, etc.) will be examined for moderating, mediating, or confounding effects.

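### The food frequency questionnaire keeps its one-year recall window when it is repeated at 3 and 6 months (and, by inference, 12), so its follow-up energy and nutrient values blend trial periods

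*Protocol article*

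**What the plan says.** Section 2.10.3 (Food consumption and nutrient intake) describes a 137-item FFQ that is to assess "habitual dietary intake over the previous year". Energy, macro- and micronutrients, fibre and bioactive compounds are to be derived from it. No other recall period is given for it.

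Section 2.10 states: "The same data collection protocol (including all study variables) applied at baseline (visit 1) will be applied at the 3-month follow-up", and the same sentence extends this to the 6-month visit. On the last visit it says: "They will be invited to attend a final data collection session at 12 months (visit 4), i.e., 6 months after visit 3". Section 2.2 says that outcomes and other relevant variables are assessed at all four time points. Neither place names the FFQ at month 12, so its use there is an inference. Table 1 lists the FFQ among the study variables.

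Follow-up diet data have stated uses:

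- Section 2.12.2 pairs dietary assessments at baseline, 3 and 6 months with vitamin E. It detects unauthorised nut eating in controls through vitamin E or through "self-reported nut intake in dietary recalls".
- The Discussion (section 3) will examine habitual diet as a moderator, mediator or confounder.
- The Discussion also says that "a fourth visit will be carried out six months after the end of the intervention to evaluate whether nut consumption and its potential effects persist".

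**The concern.** A one-year window suits baseline, where the aim is habitual diet before the trial. At follow-up the aim is diet since the trial began or, at month 12, since the nuts stopped. The window is longer than any gap between visits (3, 3 and 6 months), so each follow-up report reaches back into an earlier phase.

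The other recall windows that the article states fit the visit spacing: two weeks for BDI-II and GAD-7, one month for PSS-10 and PSQI, one week for IPAQ, and three months for the frequency items of ASSIST. The FFQ is the exception.

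At stake are the energy and nutrient values, for which the FFQ is the only source described. They would be used to see whether participants eat less of other foods to offset the added nuts, whether a nutrient carries part of the effect, and whether background diet differs between arms. The Discussion predicts maintained weight and better diet quality, so compensation is a real question in this trial.

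**Working it through.** The plan gives no figure to reproduce. The check is interval arithmetic.

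**Inputs.** Recall window 12 months (2.10.3). Visits at months 0, 3, 6 and 12 (2.2, 2.10). Intervention from month 0 to month 6 (2.2). Doses 30 and 60 g/day (2.7). Diet unrestricted after month 6 (2.10).

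**Step 1: what the window covers.** At a visit in month v the window runs from v − 12 to v. Its overlap with each period is:

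| Visit | Window (months) | Before | During | After |
|---|---|---|---|---|
| Baseline | −12 to 0 | 12 | 0 | 0 |
| Month 3 | −9 to 3 | 9 | 3 | 0 |
| Month 6 | −6 to 6 | 6 | 6 | 0 |
| Month 12 | 0 to 12 | 0 | 6 | 6 |

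**Step 2: dilution of a sustained change since baseline.** Assume literal averaging over the year.

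Reported change = true change × (months since baseline in the window) / 12

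- Month 3: 3/12 = 25%
- Month 6: 6/12 = 50%

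A difference between arms that starts at baseline is diluted by the same factor.

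**Step 3: illustration with the nuts.** Assume also full adherence, no nuts before or outside the intervention, and none after month 6.

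Reported average = dose × (months during) / 12

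| Visit | 30 g/day arm | 60 g/day arm |
|---|---|---|
| Month 3 | 30 × 3/12 = 7.5 g/day | 60 × 3/12 = 15 g/day |
| Month 6 | 30 × 6/12 = 15 g/day | 60 × 6/12 = 30 g/day |
| Month 12 | 30 × 6/12 = 15 g/day | 60 × 6/12 = 30 g/day |

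At month 6 a fully adherent 60 g participant reports the nominal dose of the other arm. At month 12 the same person reports the month-6 value although nut eating has stopped.

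**Step 4: persistence at month 12, if the FFQ is given then.** A 30 g participant who carries on at 30 g averages (30 × 6 + 30 × 6)/12 = 30 g/day. A 60 g participant who stops averages (60 × 6 + 0 × 6)/12 = 30 g/day. The FFQ value alone does not separate the two.

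**The case against.** The case against rests on five points.

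1. **Other instruments carry much of the load.** Adherence to the Mediterranean diet is scored by MEDAS, whose items are per day or per week. Table 1 lists a separate ad hoc nut questionnaire, and section 2.8 measures vitamin E at all four evaluations. A reader might infer that diet quality, control contamination and persistence of nut eating cannot be assessed at all. The documents do not support that. The dietary-quality covariate in section 2.11 is not tied to the FFQ, and the other measures address nut intake. They do not replace the FFQ for energy and nutrients: MEDAS scores nuts only as above or below a weekly threshold, the nut questionnaire covers nuts only and has no stated window, and vitamin E says nothing about energy.

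2. **Dilution is not loss.** A signal at 25% or 50% is still a signal, and those figures assume literal averaging. If respondents lean on recent diet, the true dilution is smaller. This stands: the percentages follow from the instruction as written and are not a forecast.

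3. **Month 12 is inferred, and no single visit mixes all three periods.** Both stand. Months 3 and 6 mix before and during; month 12 mixes during and after.

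4. **The limitation is already admitted.** Section 2.12.1 concedes imprecision, underreporting and recall bias. That is a general caveat, and it does not cover a fixed mismatch between recall window and visit spacing.

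5. **The dietary recalls may exist.** Section 2.10.3 announces two methods and labels only the first. The abbreviation list holds an Automated Multiple-Pass Method that the text never uses. A method may have been condensed out of the article, so it cannot be said that no recall is planned.

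**Conclusion.** The point holds for FFQ-derived energy and nutrient values at follow-up. As written, only 3 of the 12 recalled months at month 3, and 6 of 12 at month 6, fall after baseline. If the FFQ is given at month 12, half of its window is the intervention itself. Under literal averaging a sustained change appears at about 25% and then 50% of its size; with recall weighted to recent diet the loss is smaller by an amount the documents do not let one estimate.

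The follow-up values are therefore weak evidence on compensation, mediation, confounding and persistence, though not worthless. The FFQ is neither a primary nor a secondary outcome, and the intention-to-treat and per-protocol analyses in section 2.11 do not depend on it. The matter is a modest one, worth correcting because later analysis cannot recover what the wrong window failed to record.

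**What to change.** Keep the one-year window at baseline only. At later visits instruct participants to report intake since the last visit: 3 months at visit 2, 3 months at visit 3 and, if the FFQ is given at visit 4, 6 months. State whether it is given at visit 4. Give the ad hoc nut questionnaire matching windows.

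The change is one instruction on a form, and the Introduction says that recruitment has not begun. It has two costs:

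- The FFQ departs from the one-year form to which the cited reproducibility and validity figures refer. Section 2.10.3 says those figures come from an elderly population, so they transfer imperfectly to these students in any case.
- Window lengths then differ between baseline and follow-up, and raw change scores would mix true change with window length and season. Between-arm comparisons at each visit should be preferred to raw change from baseline, because all arms share the same window there.

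Separately, reconcile the dietary recalls in section 2.12.2 with the methods in section 2.10.3: either name the instrument meant or describe the recall method. This matters because, if the one-year FFQ is what is meant, a control who gave up nuts entirely at baseline would, under literal averaging, still report 9/12 = 75% of earlier intake at month 3.

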### 2.5. Participant Recruitment

Following ethics approval, authorization will be obtained from university authorities at UCLM in Cuenca, Spain. Professors will be contacted to request 15 min of class time for a brief presentation about the study, during which flyers will be distributed. Interested students can provide contact information either by giving their mobile number or scanning a QR code to complete an online form. QR codes will also be available on posters throughout the university. A research team member will then contact interested students via WhatsApp LLC (Meta Way, CA, USA) to answer questions and, if they agree to participate, schedule the baseline visit. All participants will be instructed to avoid nut consumption for at least 7 days before the baseline assessment.

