### 2.7. Intervention Implementation

Once randomization is complete, participants will receive printed and verbal standardized instructions to maintain their usual lifestyle habits throughout the study period, except for nut consumption, where the following group-specific instructions will be provided:Control group (CG): Participants will be instructed to continue their habitual diet while avoiding direct nut consumption, although the sporadic consumption of foods that may contain trace amounts of nuts as ingredients (e.g., baked goods, ice cream) does not constitute a protocol violation.Intervention groups (IG-30 and IG-60): Participants will be instructed to consume 30 g or 60 g of unsalted, unroasted mixed nuts daily and to exclusively consume the amount of nuts provided by the researchers, refraining from consuming other sources of nuts. For the participants in the CG, sporadic exposure to trace amounts of nuts in processed foods (e.g., baked goods, ice cream) will be acceptable.

The nuts (a mixture of almonds, walnuts, pistachios, and hazelnuts) will be provided free of charge, in daily portions, to participants in the intervention groups for the full duration of the trial. The participants will be asked to incorporate nuts into their usual diet and to consume them in any uncooked manner they prefer, such as alone (only nuts), with salad, or yogurt.

At months 2 and 4, participants will be instructed to collect the prepacked bags containing the daily portions of nuts required for each intervention group during the subsequent period (i.e., participants in IG-30 will receive 30 g bags, and those in IG-60 will receive 60 g bags). To maintain a single-blind design, the nuts will be provided in person for each participant by a researcher who is not involved in clinical assessments. The bags containing the daily content of nuts will be specifically produced for the trial in accordance with established quality standards and sealed under a protective atmosphere. Each bag will contain a fixed mixture of nuts in the following proportions: 35% almond, 35% walnut, 20% unshelled pistachios, and 10% hazelnut. These nut mix proportions are based on the most consumed nut types in Spain and were designed to provide a balanced profile of fatty acids, micronutrients, and bioactive compounds while reflecting habitual intake, improving palatability and adherence, and facilitating translation into practical dietary recommendations.

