Specifically, participants are awarded 1 point for adhering to specific dietary components, which includes the use of olive oil as the primary source of fat for cooking, which favors white meat over red meat and consumes the following on a daily or weekly basis: (i) 4 or more tablespoons (~13.5 g per tablespoon) of olive oil per day; (ii) 2 or more servings of vegetables per day; (iii) 3 or more servings of fruit per day; (iv) less than 1 serving of red meat or sausages per day; (v) less than 1 serving of animal fat per day; (vi) less than 1 cup (~100 milliliters) of sugar-sweetened beverages per day; (vii) 7 or more servings of red wine per week; (viii) 3 or more servings of pulses per week; (ix) 3 or more servings of fish per week; (x) fewer than 2 commercial pastries per week; (xi) 3 or more servings of nuts per week; and (xii) 2 or more servings per week of a dish featuring a traditional sauce made of tomatoes, garlic, onion, or leeks sautéed in olive oil.

The final score is the sum of each item (0–14), where a higher score indicates higher MedDiet adherence. The MEDAS score can be categorized as follows: scores < 9 indicate low adherence to the MedDiet, and scores from 9 to 14 indicate good adherence to the MedDiet [87].

Screen time: Screen time will be assessed using a self-administered questionnaire in which participants will report the number of hours they usually spend watching television, using a mobile phone, computer (for work), or other electronic devices (for leisure use) on both weekdays and weekends.

Social media addiction: Social media addiction will be measured using the short-form Social Media Addiction Scale (ARS-6), a six-item self-report instrument designed to capture core components of addictive behavior, including salience, mood modification, tolerance, conflict, and relapse, adapted to the social media context. The participants respond on a five-point Likert scale ranging from “never” to “always”, with higher scores indicating a greater risk of social media addiction [88]. This scale has been validated in adolescent and university populations, demonstrating excellent psychometric properties, including high internal consistency (Cronbach’s α = 0.923–0.950; McDonald’s ω = 0.916–0.960) [88,89].

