### 2.11. Data Management and Statistical Analysis Plan

The principal investigator will have exclusive responsibility for the data and will retain an offline copy on a secure hard drive. The anonymized data will be stored in an open-access repository (Zenodo.org) and may be shared with other researchers upon reasonable request.

The initial analytical approach will comprise descriptive statistics and data visualization to perform an exploratory assessment of the dataset, including an evaluation of bivariate associations between the predictor variables (nut consumption doses) and the outcome variables (mental health parameters). This stage will assess potential baseline differences among the three groups (CG, IG-30, and IG-60).

Subsequently, assumptions of normality and homoscedasticity for the outcome variables will be examined to ascertain the suitability of employing a repeated-measures mixed-effects model to characterize the intervention relationship between nut consumption and mental health indicators. Interpretation will focus on the magnitude and statistical significance of the fixed effects coefficients, thereby determining whether nut consumption is associated with changes in mental health outcomes and whether these associations vary across study intervention groups.

The role of BDNF will also be analyzed, examining associations between BDNF changes and mental health measures through correlation analysis at each timepoint, mediation analyses using structural equation modeling to test whether BDNF mediates the relationship between nut consumption and mental health, including cognitive improvements, and dose–response analyses across study arms. Secondary exploratory analyses will include responder analyses (BDNF increase), time-course analyses using linear mixed models, and interaction analyses examining moderators such as baseline BDNF levels and mental health status. All BDNF-cognition analyses will be designated as secondary/exploratory with appropriate adjustments for multiple comparisons and covariates, including age, sex, baseline cognitive performance, physical activity, and dietary quality.

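### The 14-point Mediterranean diet score counts the study nuts, so up to 1 point separates the arms by design: score it without nuts for arm comparisons and any post-baseline use

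*Protocol article*

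**What the plan says.** Section 2.10.3 describes MEDAS as 14 yes/no items, one of them scored for "3 or more servings of nuts per week". It continues: "The final score is the sum of each item (0–14), where a higher score indicates higher MedDiet adherence", and sets two categories: "scores < 9 indicate low adherence to the MedDiet, and scores from 9 to 14 indicate good adherence to the MedDiet".

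Section 2.7 fixes nut intake by arm. For the nut arms: "Participants will be instructed to consume 30 g or 60 g of unsalted, unroasted mixed nuts daily". Controls are told to "continue their habitual diet while avoiding direct nut consumption", with traces in processed foods tolerated.

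Section 2.10 repeats all study variables at 3 and 6 months, while the intervention is running. No section removes the nut item from the score.

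Diet quality then appears in three roles:

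- **Expected benefit.** Section 3 (Discussion) states that "the intervention is expected to improve overall diet quality", in comparison with control.
- **Covariate.** Section 2.11 lists covariates for the BDNF-cognition analyses, which it labels secondary or exploratory. The list ends with "baseline cognitive performance, physical activity, and dietary quality". Neither the diet instrument nor its time point is given.
- **Mediator, moderator or confounder.** Section 3 says that habitual dietary intake and similar variables will be examined in these roles. Section 2.10.3 and Table 1 place MEDAS in that group, not among the outcomes.

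**The concern.** A diet score that contains the treatment cannot tell whether the rest of the diet changed. If the arms are compared on the 14-item score during the intervention, the nut arms gain a point over control even when no other food differs. If the score serves as a mediator, part of the allocation passes through diet by construction and appears as an indirect effect. If a post-baseline value is a covariate in an arm contrast, part of the nut effect is assigned to the covariate.

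This touches the trial's own rationale. The Introduction says it is unclear whether the benefits seen in nut eaters come from the nuts or from accompanying habits, a better overall diet among them. A score that counts the study nuts cannot separate the two.

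**Working it through.** The plan gives no figure for this point, so there is none to reproduce. The inputs marked as assumed are not in the document.

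**1. Does allocation fix the nut item?** Inputs: 30 or 60 g per day (section 2.7), compliance at 80% of doses (section 2.8), threshold of 3 servings per week (section 2.10.3). Assumed: a serving of 25 to 30 g.

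- 30 g/day: 30 × 7 = 210 g/week, which is 210/30 = 7.0 to 210/25 = 8.4 servings.
- 30 g/day at 80%: 168 g/week, which is 5.6 to 6.7 servings.
- 60 g/day: 420 g/week, which is 14.0 to 16.8 servings; at 80%, 336 g/week or 11.2 to 13.4 servings.

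All exceed 3. A compliant nut-arm participant scores 1 and a compliant control scores 0, so the gap is 1 of 14 points. If only 80% of nut-arm participants score the item and 20% of controls do, the gap is 0.8 − 0.2 = 0.6 point.

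**2. How large is that gap on MEDAS itself?** Assumed MEDAS SD of 1.5, 2.0 or 2.5: 1/1.5 = 0.67, 1/2.0 = 0.50, 1/2.5 = 0.40 SD. This is a difference in the diet score, not a bias in a mental health outcome.

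**3. What does it do to the category at 9?** Assume the 13 non-nut items sum to a rounded normal score with mean 6 and SD 2, equal in all arms.

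- Control needs 9 from other foods: 1 − Φ((8.5 − 6)/2) = 1 − Φ(1.25) = 11%.
- Nut arms need 8: 1 − Φ((7.5 − 6)/2) = 1 − Φ(0.75) = 23%.

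Over means of 5 to 8 and SDs of 1.5 to 2.5, the gap runs from about 4 percentage points (1% against 5%) to about 26 (37% against 63%).

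**4. What would adjustment do to an arm effect?** With total post-baseline MEDAS as covariate, in SD units of the outcome:

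adjusted arm effect = total effect − b × (arm gap in the nut item), where b = r/SD is the within-arm slope of the outcome on MEDAS.

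With a gap of 1 point and assumed r of 0.1 to 0.3:

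| MEDAS SD | r = 0 | r = 0.1 | r = 0.2 | r = 0.3 |
|---|---|---|---|---|
| 1.5 | 0 | 0.067 | 0.133 | 0.200 |
| 2.0 | 0 | 0.050 | 0.100 | 0.150 |
| 2.5 | 0 | 0.040 | 0.080 | 0.120 |

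For r above zero the shift is 0.04 to 0.20 SD. Against an illustrative effect of 0.5 SD, that is 0.04/0.5 = 8% to 0.20/0.5 = 40%.

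A simulation with 200,000 participants per arm (true effect 0.5 SD, MEDAS SD 2, r = 0.2) agrees:

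| Covariate | Arm effect |
|---|---|
| None | 0.501 |
| Post-baseline MEDAS, 14 items | 0.403 |
| Post-baseline MEDAS without the nut item | 0.502 |
| MEDAS before allocation | 0.502 |

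In a mediation model with the 14-item score, the difference 0.501 − 0.403 = 0.098 SD would be reported as an effect through diet, although no other food changed in the simulation.

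**The case against.** The strongest reply concerns scope. The covariate list in section 2.11 belongs to the exploratory BDNF-cognition analyses. The only covariates named for the repeated-measures mixed models are examination periods and seasons (section 2.12.2). A reader might infer that the primary nut effect is adjusted away; the document does not support that. Several BDNF-cognition analyses are also not arm contrasts, and adjusting a correlation between BDNF and cognition for diet removes no nut effect. This objection stands.

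The document also never says that dietary quality means MEDAS, and the word baseline in "baseline cognitive performance, physical activity, and dietary quality" can be read as covering all three items. Both remarks are fair, so over-adjustment is a risk and not a stated plan. They do not answer the arm comparison. MEDAS is the only diet score described, and the food frequency questionnaire in section 2.10.3 counts nuts too.

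One may add that the expected diet benefit is a sentence in the Discussion, that no between-arm MEDAS test is specified, and that eating nuts is a real improvement on an index that rewards nuts. That is right as far as it goes. Such a result would not be false, but it would say nothing about the rest of the diet.

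A reader might also suspect the avoidance period before baseline: "All participants will be instructed to avoid nut consumption for at least 7 days before the baseline assessment". It applies to every arm and creates no arm difference by itself. The gap during the intervention is up to 1 point whatever the earlier intake.

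**Conclusion.** The point holds with limits. The nut item is set by allocation, is re-measured during the intervention and is not excluded. If diet quality is read from MEDAS, up to 1 of 14 points of the expected benefit over control is the intervention itself (0.6 point under the weaker compliance assumed above). Any post-baseline use as mediator or confounder partly re-measures treatment.

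Over-adjustment is confined to exploratory BDNF-cognition analyses that contrast arms, and arises only with a post-baseline value. It would be about 0.04 to 0.20 SD under the assumed correlations and SDs, and zero if r = 0 or if the covariate precedes allocation.

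The 0.40 to 0.67 SD gap on MEDAS is close to the 0.5 used in section 2.4. A reader might therefore infer a bias of that size in the trial's results. It is not one: section 2.4 concerns the primary outcome, and the gap is in the diet score.

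**What to change.** - Name the instrument and time point meant by dietary quality in section 2.11.
- Score MEDAS without the nut item (0 to 13) for comparisons between arms and for any post-baseline use as covariate or mediator.
- In arm contrasts, adjust only for diet quality and physical activity measured before allocation.
- Keep the 14-item score to describe the baseline sample and for baseline moderator analyses, where habitual nut intake is useful information.
- Reconcile section 2.6, which randomises before the baseline assessment and informs participants at once, with section 3, which says allocation is concealed until baseline assessments are completed. Only then is a baseline value certain to precede allocation.

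The cost is wording. Table 1 already lists the specific components of MEDAS, so no new data are needed, and the article states that it precedes recruitment. The small downside is that the published cut of 9 does not apply to a 13-item score.
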